#### Adherence / non-adherence

Reasons for non-adherence will be recorded after each session through standardized questions: “how much difficulty did you have completing the session?”, “What factors made therapy difficult?”, and “any other important message?”. Patients’ experiences and suggestions are investigated by means of weekly interviews with standardized open-ended questions. The possible impact of the emotional relationship between client and therapist as well as the degree of agreement on therapy goals and tasks is assessed after 8 weeks of training using the Dutch version of the work-alliance questionnaire (WAV-12) [57]. Finally, side effects of HD-tDCS are surveyed and documented after each session by means of standardized questions.

Conclusions will be based on the comparison of the change in score at 8 weeks versus baseline in the 3 arms. Averages and standard deviations will be used as aggregation methods for all outcome measurements.

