## Introduction

### Background and rationale {6a}

Dysphagia is considered to be one of the most severe functional impairments in head and neck cancer (HNC) survivors treated with radiation (RT) or chemoradiation (CRT) [1–3]. Radiation-associated dysphagia (RAD) may occur temporarily as an acute side effect during or immediately after treatment. However, it may also become chronic (C-RAD) or develop several years post-treatment (Late RAD) [4–6].

Reported prevalence rates for RAD extend to 95% during treatment and around 70% 12 months to more than 10 years post-treatment [1, 7]. Acute toxicities such as oedema, mucositis, and xerostomia typically develop during or immediately after CRT, but generally improve in the following months post-treatment [5, 6]. In contrast, tissue fibrosis and loss of muscle fibers (atrophy) may occur and persist long after completion of the treatment due to decreased blood supply to the muscles which can result in a reduced range of motion and strength [8–10]. Disturbed neurotransmission and lower cranial neuropathies are also important late side effects of chemoradiation causing C-RAD [8, 11–13]. These late effects lead to impairment of crucial swallowing structures affecting both the oral and pharyngeal phase of swallowing resulting in malnutrition, dehydration, and aspiration. Further disuse will enhance the deterioration of muscle fibers, causing a vicious cycle affecting the patient’s health and quality of life [1, 2, 14, 15]. Furthermore, the risk for developing life-threatening aspiration pneumonia is high since the majority of dysphagic HNC survivors seems to aspirate silently [1].

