**Fig. 4 Fig4:**
[figure not shown]
Expiratory Muscle Strength Trainer (EMST150 device, Aspire Products, Gainesville, Florida, USA)

The different exercises described above alternate during the sessions. Participants will start with TSE the first day and perform CTAR and EMST the following day.

The *second* and *third* group receive a combination of 4 weeks strength training followed by 4 weeks functional swallowing therapy. The strengthening exercises in groups 2 and 3 are the same as in group 1. Functional swallow therapy involves exercise-based practice with swallowing consistencies that challenge the patients’ entire swallowing system by progressively increasing the volume and viscosity of the bolus and hence increasing the required effort to swallow the bolus as described in the McNeil Dysphagia Therapy Program (MDTP) [31]. In MDTP, a food hierarchy is used to gradually increase the volume, consistency, intensity, and timing of swallowing in a standardized manner. Participants start at a certain level and move forward with a series of successful swallows or backwards with a series of unsuccessful swallows. The starting level is considered to be the most advanced level of consistency a patient can swallow safely, determined based on an instrumental swallowing assessment (fiberoptic endoscopic evaluation of swallowing, FEES).

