### Criteria for discontinuing or modifying allocated interventions {11b}

tDCS has been thoroughly investigated and is considered to be safe [46]. The tolerability of HD-tDCS is supported by studies using intensities as high as 2.0 mA for up to 20 min [49]. The possible side effects of HD-tDCS are assessed systematically in this study using a standardized questionnaire. Expected side effects are mild to moderate and limited to skin lesions under the electrodes, mild tingling or itching sensations, and transient redness. If the participant experiences a high degree of pain or discomfort, a rest day will be scheduled. Patients will still perform strength or functional training exercises that day but without receiving HD-tDCS. When the described complaints remain present, the treatment will be stopped after further consideration with the patient and members of the study group. All reported side effects related to the HD-tDCS will be analyzed and reported in future publications.

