### Composition of the data monitoring committee, its role and reporting structure {21a}

Poreisz et al. summarized the adverse events of 567 tDCS sessions over motor and non-motor cortical areas, showing relatively minor adverse effects. None of the subjects requested to terminate the stimulation or needed medical assistance during or after the application [65]. Side effects of HD-tDCS described in the literature also include mild tingling, temporary redness, and mild pain due to the electrodes [49]. As the experimental interventions are very low-risk, no data monitoring committee will be formed.

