### Adverse event reporting and harms {22}

Participants are encouraged to report any adverse events immediately to the research team. They have the possibility of withdrawing their participation at any time in case serious adverse events occur. Detailed records of all adverse events are maintained and reported in accordance with legal and regulatory requirements. Serious adverse events are reviewed by an appropriate committee for the monitoring of trial safety. Suspected unexpected serious adverse reactions (SUSAR) are identified and fully reported to the regulatory authority and the central ethics committee within the required timelines.

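### Standardized harm questions cover HD-tDCS only, so respiratory events depend mainly on participants reporting them and may be under-recorded

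*Protocol article*

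**What the plan says.** Stimulation harms are collected actively. Under Criteria for discontinuing or modifying allocated interventions {11b}: "The possible side effects of HD-tDCS are assessed systematically in this study using a standardized questionnaire". Under Adherence / non-adherence the timing is given: "side effects of HD-tDCS are surveyed and documented after each session by means of standardized questions". Section {11b} also commits to publication: "All reported side effects related to the HD-tDCS will be analyzed and reported in future publications".

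For all other events, Adverse event reporting and harms {22} says "Participants are encouraged to report any adverse events immediately to the research team", and then "Detailed records of all adverse events are maintained and reported in accordance with legal and regulatory requirements". It adds that a committee for trial safety reviews serious events. Neither the reporting route nor the record keeping is limited to an arm or to stimulation.

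On risk, Background and rationale {6a} states that "the risk for developing life-threatening aspiration pneumonia is high since the majority of dysphagic HNC survivors seems to aspirate silently". The functional therapy given to groups 2 and 3 in their last four weeks works by "progressively increasing the volume and viscosity of the bolus" (Intervention description {11a}). The data monitoring committee section {21a} summarizes tDCS and HD-tDCS studies and concludes: "As the experimental interventions are very low-risk, no data monitoring committee will be formed".

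**The concern.** Active questioning is aimed at the component whose expected effects the article itself describes as mild to moderate. The event that the Background singles out as life-threatening has no solicited item and is not named as an outcome. The exercise content also differs between arms in a way that bears on this event: group 1 does strengthening for eight weeks, while groups 2 and 3 move to progressive swallowing practice after week 4.

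Two things are at stake. First, some respiratory events may never reach the records, because a record can hold only what becomes known. Second, groups 2 and 3 are asked about side effects after each stimulation session, up to 32 times, and group 1 has no stated counterpart. Repeated side-effect questions may lead participants to mention other events as well. The primary FOIS analysis is not affected. What is affected is the safety account of the exercise programs in a trial whose Objectives {7} ask for programs that are tolerable as well as effective.

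**Working it through.** The plan states no figure on this point, so the main check is to set the sections side by side.

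**1. Who is asked what**

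| Source of harm information | Group 1 | Group 2 | Group 3 | Aimed at harms? |
|---|---|---|---|---|
| HD-tDCS side-effect questionnaire, each session ({11b}, Adherence / non-adherence) | no | yes (sham) | yes | yes, stimulation only |
| Participant-initiated adverse event reports {22} | yes | yes | yes | yes, but unprompted |
| Session questions on difficulty, its causes and any other message | yes | yes | yes | no |
| Weekly interviews on experiences and suggestions | yes | yes | yes | no |
| Therapist present at every session {11c} | yes | yes | yes | no stated harm check |
| Endoscopy with PAS at baseline, weeks 4 and 8, and 4 weeks after the last session | yes | yes | yes | swallowing outcome, not clinical events |

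The entry for group 2 in the first row is an inference: sham participants follow the same stimulation procedure and are blinded, so they must get the same questions. The number of sessions is 4 per week × 8 weeks = 32.

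**2. What the table shows.** For respiratory events the stated route is the same in all three arms. The arms differ in whether a harm-specific questionnaire is put to them at all. Incomplete capture of respiratory events is therefore possible in every arm. Uneven capture is possible only indirectly, through the extra prompting in groups 2 and 3.

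**3. Illustration under assumed rates.** The documents give neither an event rate nor a capture rate. Let p be the true risk per patient, s the fraction of events captured, and n the number of patients. Then P(at least one recorded event) = 1 − (1 − p·s)^n.

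| Assumed p | n = 35, s = 1 | n = 35, s = 0.5 | n = 70, s = 1 | n = 70, s = 0.5 |
|---|---|---|---|---|
| 2% | 51% | 30% | 76% | 51% |
| 5% | 83% | 59% | 97% | 83% |
| 10% | 97% | 83% | 99.9% | 97% |

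Example: 1 − (1 − 0.05 × 0.5)^35 = 1 − 0.975^35 = 0.59. Here n = 35 is one arm and n = 70 is groups 2 and 3 together.

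**4. Effect on a comparison.** With the same s in both arms, the recorded risk difference is s·(p₂ − p₁), so at s = 0.5 it is half the true one. With equal true risk of 5% but s = 0.5 in group 1 and s = 1 in group 2, the expected recorded counts are 35 × 0.05 × 0.5 = 0.875 and 35 × 0.05 × 1 = 1.75. That is an apparent doubling with no true difference. Both cases are hypothetical.

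**5. A figure that does not bear on the point.** With zero events and full capture, the one-sided 95% upper bound on risk is 1 − 0.05^(1/35) = 8.2% in one arm and 1 − 0.05^(1/70) = 4.2% in groups 2 and 3 together. These limits come from the sample size, and better questioning would not change them.

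**The case against.** The strongest reply is that this is an article condensing a fuller protocol. Adverse event forms and item lists commonly sit in the full protocol, the case report forms or the instruction manual, none of which is shown. That limits the point: what the trial staff actually ask is unknown. It does not remove it, because the article states a collection method, active for stimulation and participant-initiated for the rest, and that stated method can be improved.

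Second, participants are not left alone with their symptoms. A therapist attends every session, an open question follows each one, there are weekly interviews and daily counselling, and serious events go to a safety committee. This stands, so it would be wrong to say that detection is purely spontaneous. But none of these contacts is described as asking about chest infection, antibiotics or admission, and therapy sessions stop after week 8.

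Third, functional therapy starts at a consistency judged safe on endoscopy and steps back after unsuccessful swallows. This also stands. It concerns how risk is managed, not how events are recorded.

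Fourth, a reader might infer from the Background that pneumonia itself goes unnoticed and is the event least likely to be volunteered. The text says that aspiration is often silent; it does not say so of pneumonia. Silent aspiration is also what the scheduled endoscopy with PAS can show, in all arms.

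**Conclusion.** The point holds as a risk to ascertainment that is cheap to remove. The article fixes standardized harm solicitation for HD-tDCS only, which reaches groups 2 and 3 but not group 1. Respiratory events rest on participant reports plus general questions, although the article rates the pneumonia risk as high and gives progressive bolus training to two arms only. Its low-risk statement is supported by stimulation literature alone and does not address the exercise or functional components.

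A reader might go further and infer that harm data in the exercise comparison are already unequal and incomplete, or that a fair comparison is impossible. The documents do not support this. The stated route for respiratory events is identical across arms, carry-over from side-effect prompting is conjecture, and Sample size {14} plans three pairwise comparisons without naming a main one.

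The size cannot be fixed from the documents. With assumed risks of 2% to 10% and assumed half capture, the chance of recording any event in an arm of 35 falls by 14 to 25 percentage points (51% to 30%, 83% to 59%, 97% to 83%). These figures rest wholly on the assumed rates.

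**What to change.** Add a short fixed set of respiratory items to the existing session questions and to the week-12 visit: chest infection or pneumonia, fever with cough, antibiotics for a chest infection, and hospital admission. Ask them in identical words in all three arms. Have the week-12 questions cover the four weeks without sessions. Tabulate the events by arm, and show worsening of the already collected PAS score next to them.

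Restate the rationale in {21a} so that it covers strengthening and functional training as well as stimulation. Reconcile it with the risk described in {6a}, and identify the safety committee mentioned in {22}, given that {21a} says no data monitoring committee will be formed.

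The cost is a slightly longer session form and one extra table. No new visit, procedure or staff is needed, and no treatment rule changes. If recruitment is already under way when the items are added, record the date of the change and report events before and after it separately, because capture will differ between the two periods.

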### Confounders

#### Patients, disease and therapy characteristics

Patient and situational characteristics in particular age, gender, educational level, social status, personality traits (using the NEO-Five Factor Inventory (NEO-FFI) [58]), frailty (using the Clinical Frailty Scale (CFS) [39]) handedness [59], and dental condition (using the Oral Health Assessment Tool (OHAT)) are examined at baseline [60]. Disease characteristics include location and stage of the carcinoma, TNM classification, HPV status (based on p16 immunohistochemistry; cut-off > 70% cytoplasmatic and nuclear staining [61]), complaints of xerostomia [62], and thicky saliva (VAS). Treatment-related information is assessed, i.e., chemotherapy, fractionation, bilateral neck irradiation, duration, and time post-treatment. This information is gained at baseline by radiation oncologists, head and neck surgeons, and otolaryngologists.

#### Attitudes about exercises

Participants’ attitudes on exercises are investigated weekly during training using a standardized questionnaire developed by Sluijs et al. [63].

### Participant timeline {13}

All participants will be assessed using the scales described above at baseline, weekly during therapy, after 4 and 8 weeks of therapy, and 4 weeks after the last therapy session. Table 1 gives an overview of study assessments at different timepoints.

### Sample size {14}

The primary conclusions of this study will be based on a linear mixed effects model with post hoc comparisons. For the sample size calculation, this analysis was simplified to 3 pairwise comparisons at week 8 by means of independent samples *t*-tests. Based on Carnaby-Mann et al., we assume a change in Functional Oral Intake Scale (FOIS) after 8 weeks of 2.5 with a standard deviation (SD) of 1.7 in group 2 [31]; based on our own experience, we expect little effect in group 1 (change = 1 with same SD). With these numbers in mind, we want to be able to detect a difference of 1.5 change in FOIS between any 2 groups, with a SD of 1.7. Therefore, we need to include 31 patients per group to achieve 80% power at a significance level of 0.017. A Bonferroni correction for multiple testing was applied to the significance level, as three comparisons will be made (between the 3 groups). To cover for drop-out, we add 4 extra subjects per group. In conclusion, a total sample size of 105 participants (*n* = 35/group), taking into account drop-outs, is needed to demonstrate a statistically significant difference. The software PASS 11 is used to estimate the sample size.

### Recruitment {15}

Recruitment of eligible subjects will be done by the appointed researchers during the multidisciplinary oncological follow-up consultations in the University hospitals of Leuven, Antwerp, and Ghent and in the Sint-Augustinus Hospital. All patients treated with primary RT or CRT who are at least 6 months post-treatment are referred to the researchers for completion of the EAT-10 and FOIS. If a patient appears eligible to participate based on these measurements, the study will be explained in more detail. Participants who are interested in taking part are further assessed for eligibility. Patients who are in doubt about participation receive a folder with information about the study and contact details. If a participant agrees to participate, the informed consent is signed before the baseline measurements are performed by the researcher of each center.

The participating centers have a high level of expertise in the field of head and neck cancer and dysphagia research. Data collection in these hospitals enables the study to include an adequate amount of patients to obtain sufficient power.

## Assignment of interventions: allocation

### Sequence generation {16a}

Patients who are eligible according to the inclusion criteria and signed the informed consent form are randomly assigned to one of the three groups with a 1:1:1 allocation using the program Qminim, an online minimization service supported by the Information and Communication Technology (ICT) Unit of the Antwerp University Hospital. Selected minimization factors include center, FOIS score (level 1 or 2 for more than 3 months, level 1 or 2 for less than 3 months, levels 3 to 6), and time between completion RT or CRT and beginning of the therapy program (< 1 year post Tx, between 1 and 5 years post Tx, > 5 years post Tx).

### Concealment mechanism {16b}

The assignment is performed automatically in real-time based on these criteria. Researchers of each center have access to the program but do not have any precognition of the randomization. Since this is a single-blinded study, minimization and outcome assessment for groups 2 and 3 will be blinded for the participants.

### Implementation {16c}

The SLPs and medical staff who enrol eligible participants will enter the minimization factors in Qminim.

## Assignment of interventions: blinding

### Who will be blinded {17a}

Since this is a single-blinded study, minimization and outcome assessment for groups 2 and 3 will be blinded for the participants. The statistician and 2 independent doctors who will rate the FEES videos after completion of the study are blinded to the real or sham HD-tDCS intervention. No other parties are blinded to the real or sham HD-tDCS intervention.

### Procedure for unblinding if needed {17b}

Not applicable. The allocated intervention will not be revealed to participants during the trial.

## Data collection and management

### Plans for assessment and collection of outcomes {18a}

Before recruitment, all researchers will receive an instruction manual and a presentation of the study to ensure consistency and standardization of data collection and assessment. All data are recorded in case report forms (CRFs) by the data collectors during baseline, treatment, and upon completion of the treatment and follow-up phase. Physicians will be trained to apply the assessment tools required for this study ensuring accurate and thorough collection of data. The CRFs will be read repeatedly before the start of the study. Uniform agreements will also be made in advance regarding the use of the strength training equipment. Furthermore, the SLPs completed a course to obtain certification for treating patients following the MDTP guidelines and attended several training sessions for administering HD-tDCS.

### Plans to promote participant retention and complete follow-up {18b}

Participants receive daily counselling and are motivated to continue their participation. The home-based treatment protocol at a frequency of four times a week is likely to have a positive impact on patients’ adherence. Appointments are scheduled and shared well in advance. Hospital appointments are reminded at least 2 days in advance. Participants are followed up once, 4 weeks after the last therapy session. This follow-up appointment, if possible, is scheduled together with other follow-up appointments in the hospital.

### Data management {19}

Datasets are entered and stored in a non-publicly available repository. All clinical record forms are managed using REDCap (Research Electronic Data Capture), supported by the ICT department of the Antwerp University Hospital [64]. Redcap is a secure web application designed to support data capture for research studies. Both the printed CRFs and electronic data will be locked in order to avoid that adjustments can be made after the data has been recorded. The researchers of each participating institution have access to the data of their patients. The Principal Investigator and the first author have access to all collected data.

### Confidentiality {27}

All data is pseudonymized, encoded, and securely stored for 30 years. Identifying patients’ information will be saved on the secure server of each research center which only the researcher of the particular center will have access to.

### Plans for collection, laboratory evaluation, and storage of biological specimens for genetic or molecular analysis in this trial/future use {33}

This RCT does not require collection of biological specimens.

## Statistical methods

### Statistical methods for primary and secondary outcomes {20a} and methods for additional analyses (e.g. subgroup analyses) {20b}

The primary conclusions of this project will be based on the intent to treat population. All patients will be analyzed in the treatment group they were assigned to. Patients who withdraw consent for use of their data will not be included in any analysis.

Data will be analyzed using a repeated measures analysis with post hoc testing, using the most recent version of IBM SPSS Statistics (V27.0) and R software. Evaluation of the primary endpoint will be performed using a linear mixed effects model with a random intercept per subject and fixed effects of group, time (categorical with 4 categories: baseline, 4 weeks, 8 weeks, and 12 weeks), and interaction between time and group. Based on this model, post hoc comparisons will be performed. The primary conclusion will be based on the comparison of the change at 8 weeks versus baseline in the three arms. Bonferroni-Holm correction for multiple testing will be applied here.

Additionally, linear, logistic, and binary mixed effects models with random intercept, fixed group, time (categorical), and time by group interaction will be used to evaluate the differences in all secondary outcome measures over time in the three groups. For linear mixed effects models coefficients, standard errors and p-values will be reported. For logistic and ordinal logistic mixed models, odds ratios, 95% confidence intervals, and p-values will be given.

Post hoc comparisons will be made based on these models. Confounders can be added to the model.

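### The random-intercept-only primary model pools the error of the week-8 change over all six visit pairs, so type I error for the primary comparisons rests on an unverified covariance assumption

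*Protocol article*

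**What the plan says.** The section Statistical methods {20a}/{20b} names a "linear mixed effects model with a random intercept per subject and fixed effects of group, time", with "time (categorical with 4 categories: baseline, 4 weeks, 8 weeks, and 12 weeks") and a time-by-group interaction. The target is fixed there too: "The primary conclusion will be based on the comparison of the change at 8 weeks versus baseline in the three arms". On multiplicity it says "Bonferroni-Holm correction for multiple testing will be applied here". No residual covariance structure, further random effect or robust standard error is named, and the secondary mixed models are also given a random intercept.

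Sample size {14} says "this analysis was simplified to 3 pairwise comparisons at week 8 by means of independent samples" t-tests, aiming to "detect a difference of 1.5 change in FOIS between any 2 groups, with a SD of 1.7", with "80% power at a significance level of 0.017". That SD of the week-8 change is the only variability figure in the article.

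**The concern.** A random intercept with independent residuals implies compound symmetry: equal variance at every visit and equal correlation between every pair of visits. One residual variance then serves all differences between visits, yet the primary conclusion uses only one of them, baseline to week 8.

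If that difference varies more than the average pair, its standard error is too small and the Holm-adjusted p-values are too small in all three comparisons. If it varies less, the test is conservative and power is lost. Holm controls the familywise rate only when the p-values fed into it are valid.

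The contrast spans two visit intervals. Over the six pairs the mean span is (3x1 + 2x2 + 1x3)/6 = 1.67 intervals. If correlation decays with time, the error therefore goes in the anti-conservative direction.

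**Working it through.** **Plan's own figure.** Inputs from Sample size {14}: difference 1.5, SD 1.7, alpha 0.017 (taken as two-sided), power 80%. The normal formula gives n = 2 x (1.7/1.5)² x (2.387 + 0.842)² = 2 x 1.284 x 10.42 = 26.8, so 27. The exact noncentral t gives 29. The article says "we need to include 31 patients per group", which has 84% power by t-test, so the planned number is adequate on its own terms. That calculation uses the variance of the change itself, whereas the mixed model does not estimate this variance separately.

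**Bias ratio.** For balanced data the model's residual variance estimates half the mean variance of the six pairwise visit differences. With n per arm:

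- model variance of the contrast = (mean of the six difference variances) x 2/n
- true variance = Var(Y8 − Y0) x 2/n
- r = Var(Y8 − Y0) / (mean of the six), and model SE / true SE = 1/√r

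**Example, AR(1) with rho 0.7 and unit variances.** The difference variance at lag k is 2(1 − 0.7^k): 0.60 (three pairs), 1.02 (two pairs) and 1.314 (one pair). The mean is (1.80 + 2.04 + 1.314)/6 = 0.859, so r = 1.02/0.859 = 1.19 and 1/√r = 0.918. The standard error is 8% too small.

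**Example tied to the plan's SD of 1.7.** Suppose patients differ in response with SD s, half the response appears by week 4 and all of it by week 8, it then holds, and the rest of the change variance is independent visit noise. The six squared response steps sum to 0.25 + 1 + 1 + 0.25 + 0.25 + 0 = 2.75, a mean of 0.458. Then r = 2.89 / (2.89 − 0.542 s²).

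- s = 1.0: r = 2.89/2.348 = 1.23
- s = 1.5: r = 2.89/1.671 = 1.73

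**From r to familywise error (global null, Holm, nominal 5% overall).** At r = 1.00, 1.06, 1.2, 1.3, 1.5 and 1.7 the error is 4.2%, 5.0%, 7.1%, 8.7%, 12.1% and 15.4%. Three correlated comparisons leave some slack, so 5% is passed only above r of about 1.06. In the plateau example that threshold is reached at s² = 2.89 x (1 − 1/1.06)/0.542 = 0.30, about 10% of the change variance.

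**Simulation.** 31 per arm, complete normal data, 40,000 runs. All covariances are assumed.

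| Assumed pattern | r | Model SE / true SE | Familywise error, random intercept | Same, using variance of the change |
|---|---|---|---|---|
| Compound symmetry | 1.00 | 1.00 | 4.3% | 4.3% |
| AR(1), rho 0.5 to 0.9 | 1.16–1.20 | 0.928–0.913 | 6.7–7.2% | 4.1–4.5% |
| Intercept + AR(1) + noise | 1.09 | 0.96 | 5.6% | 4.3% |
| Random slope + noise | 1.11 | 0.95 | 6.0% | 4.3% |
| Differing response (SD 1.5), then plateau | 1.53–1.73 | 0.81–0.76 | 13–17% | 4.4% |
| Differing response, partial regression by week 12 | 2.08 | 0.69 | 22% | 4.4% |
| SDs rising 1.2 to 1.7, equal correlation | 0.96 | 1.02 | 3.9% | 4.4% |
| Noisier week 4 | 0.80 | 1.12 | 2.0% | 4.3% |
| Noisier week 12 | 0.64 | 1.25 | 0.9% | 4.5% |

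A further simulation used integer scores from 1 to 7 with baseline capped at 6, response SD 1.0 to 1.5 and a plateau after week 8 (20,000 runs). Familywise error was 8.7% to 17.2% with the random intercept and 4.2% to 4.4% with the variance of the change.

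**Partial null.** If group 1 differs from both other groups and those two nulls are rejected, Holm tests the remaining comparison at 5% and the slack is gone. At r = 1.2 the error is 2 x [1 − Φ(1.96/√1.2)] = 7.4%.

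**The case against.** The strongest reply is that the article contains no covariance information beyond the SD of 1.7, so neither direction nor size is established. That stands. Two ordinary patterns give only 5.6% and 6.0%, and several plausible ones are conservative.

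Two arguments that might seem to settle the direction do not:

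- **Restricted baseline spread.** Eligibility might be thought to narrow baseline FOIS and so worsen the problem. With assumed SDs of 1.2 at baseline and 1.7 later, equal correlation of 0.6 gives baseline differences of 1.44 + 2.89 − 2 x 0.6 x 2.04 = 1.88 and later ones of 2 x 2.89 x 0.4 = 2.31. Then r = 1.88/2.10 = 0.90, with familywise error of 3.1% to 3.3% for correlations of 0.5 to 0.7. With AR(1) at rho 0.7 it is about 5.3%. Restriction therefore offsets inflation. Entry by EAT-10 and/or FOIS also means the FOIS limit need not bind every patient.
- **Stability after therapy.** Weeks 8 to 12 might be taken as a quiet interval. Objectives {7} makes detraining a question of the trial, so stability cannot be assumed. Detraining can move r either way.

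A serial residual structure could also sit beside the random intercept in an analysis plan not shown here. That is possible. But the article affirmatively names the random effect for the primary analysis, and as worded it is the only source of within-patient correlation, so the stated choice is open to comment. The use of t-tests for planning is no separate fault, because the article says openly that it is a simplification.

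**Conclusion.** The point holds in a limited form, with moderate confidence. The algebra is exact: as worded, the model's standard error for the primary contrast is correct only when the variance of the baseline-to-week-8 change equals the six-pair average. Nothing in the article supports that equality.

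The consequences are conditional on assumed covariances. Familywise error is about 7% under AR(1) with equal variances and roughly 7% to 13% or more with differing response and a plateau. It is near 4% to 5% under compound symmetry and below 5% under some other patterns, at a cost in power.

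A reader might infer that the 5% rate will be exceeded. The documents do not support that: they give no correlations, Holm's slack absorbs r up to about 1.06 under the global null, and conservative patterns exist. The 5% familywise level is itself implied by 3 x 0.017 and not stated. Most of the figures also assume complete normal data, whereas FOIS is a bounded 7-point scale. The supported conclusion is that type I error is unprotected, which makes this a recommended improvement and not a demonstrated failure.

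**What to change.** For FOIS and the other continuous outcomes, replace the random intercept with an unstructured 4x4 within-subject covariance across baseline and weeks 4, 8 and 12, with Kenward-Roger or Satterthwaite degrees of freedom. Keep the fixed effects, the week-8 contrast and Holm as they are. State the fallback in advance in case the model does not converge: heterogeneous Toeplitz, or the random intercept with cluster-robust standard errors.

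The cost is about one sentence of text and 4 x 5/2 = 10 covariance parameters instead of 2, which 105 patients can support. No extra patients or data are needed. When the variance of the week-8 change itself was used, simulated familywise error stayed between 4.1% and 4.5% in every pattern in the table. The change should be made before any unblinded analysis.
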